#### Health economic analysis

The economic evaluation will assess the cost-effectiveness of the three competing interventions. The analysis will be conducted from the perspective of the UK National Health Services (NHS) and Personal Social Services (PSS). A health economics analysis plan (HEAP) will be written, and agreed with the oversight committees, before any analyses are undertaken. Any subsequent amendments to the plan will be clearly documented.

Self-reported questionnaires and hospital forms will be used to evaluate resource use and associated costs over the follow-up of the trial. Cost components will compromise hospital stay (initial and subsequent inpatient episodes, outpatient hospital visits and A&E hospital admissions) and primary care consultations (e.g. GP, nurse and physiotherapy). An accurate record of procedures at the hospital level (e.g. centres in the trial) will be put in place to record per patient information (e.g. surgical procedures, complications related to the surgical intervention, and other medical complications). Costs relating to surgical procedures will be based on time in theatre, staff time, consumables and devices, and nights in hospital after the procedure. These data will be collected via a form that will be specifically designed for this trial. Similarly, physiotherapy treatment logs will be completed by physiotherapists providing patient care. Cost components for health resource use will be derived from established national costing sources such as NHS Reference Costs [37], PSSRU Unit costs of health and social care [38], and the British National Formulary [39]. Unit costs will be multiplied by resource use to obtain a total cost for each patient.

The primary outcome for the economic analysis will be the additional cost per quality-adjusted life year gained (QALY). Value for money will therefore be estimated in terms of cost per QALY following an intention-to-treat approach using EQ-5D-5L data. The EQ-5D-5L will be collected at Baseline, 6 months, 12 months and 24 months’ follow-up. The overall difference in EQ-5D index scores between the two arms will be examined through regression methods, consistent with the model selected in the statistical analysis. The EQ-5D health states will be valued using the mapping function developed by van Hout et al. [40] and following the NICE position statement [41] QALYs will be calculated by plotting the utility scores at each of the three time points and estimating the area under the curve [42]. A discount rate will be applied to all costs and QALYs accrued after 12 months at a rate of 3.5% per annum in line with NICE guidance [43].

For the analysis, regression methods will be used to allow for differences in prognostic variables. Incremental cost-effectiveness ratios and net-benefit statistics will be calculated. The pattern of missing data will be analysed and handled by means of multiple imputation (MI) [44]. A range of sensitivity analyses will be conducted to test the robustness of the results under different scenarios, including probabilistic sensitivity analysis. In case of positive results of the trial, we will recommend that costs and outcomes will be extrapolated and modelled over a longer time horizon than captured by the trial (e.g. lifetime of the patient).

### Plans to give access to the full protocol, participant-level data and statistical code {31c}

This manuscript constitutes a complete representation of the trial protocol. The full protocol and related documents for the PROFHER-2 trial are available on the NIHR website [45]. Anonymised participant-level data may be requested from YTU after trial completion — the approval of any data requests is at the discretion of the Chief Investigator and YTU.

## Oversight and monitoring

### Composition of the coordinating centre and trial steering committee {5d}

#### Trial Coordination

The coordination of the PROFHER-2 trial will be managed by YTU in collaboration with the sponsor and chief investigator. The YTU team will include the trial manager, trial coordinators, data management and support staff.

#### Trial Management Group

The PROFHER-2 trial management group will include the sponsor, chief investigator, co-applicants (clinicians and other researchers), patient representatives, the trial manager, trial coordinators, statisticians, and health economists. The management group will meet every 3 months throughout the duration of the trial.

#### Trial Steering Committee

The PROFHER-2 trial steering committee (TSC) will include an independent chair, two independent clinical members with experience relevant to the trial, and a patient representative. They will meet at least once a year throughout the duration of the trial.

### Composition of the data monitoring committee, its role and reporting structure {21a}

The PROFHER-2 data monitoring committee (DMC) will be composed of members independent of the sponsor and trial team and will include an orthopaedic surgeon, a statistician, and one other clinician.

The DMC will meet at least once a year throughout the trial and will report to the TSC.

### Adverse event reporting and harms {22}

Adverse events (AEs) are defined as any untoward medical occurrence (i.e. any unfavourable and unintended sign, symptom or disease), experienced by a trial participant and which is temporarily associated with the study treatment (interventions or control) and is related to the affected shoulder or to the study interventions or control treatments.

AEs, which might be expected with this injury and its treatments include surgical site infection, dislocation/instability, haematoma, neurovascular injury including axillary nerve palsy, pain including complex regional pain syndrome, delayed wound healing and/or wound dehiscence, intraoperative fracture, acromial stress fracture, scapular notching, heterotopic ossification, implant loosening or failure and humeral bone loss [12, 15, 46]. Additionally, AEs associated with anaesthesia such as cerebrovascular events, cardiovascular events including venous thromboembolism, urinary retention and respiratory tract infection can also be expected in this patient group.

Serious AEs (SAEs) are defined as any untoward and unexpected medical occurrence that:Results in deathIs life-threateningRequires hospitalisation or prolongation of existing inpatients’ hospitalisationResults in persistent or significant disability or incapacityIs a congenital anomaly or birth defectAny other important medical condition that, although not included in the above, may require medical or surgical intervention to prevent one of the outcomes listed

For the purposes of the PROFHER-2 Trial, the following are not considered a SAE but will be considered an adverse event:Complications of anaesthesia or surgery (e.g., wound complications, infection, damage to a nerve or blood vessel and thromboembolic events)Secondary operations for infection; dislocation or instability; malunion; non-union; peri-prosthetic fracture; or for symptoms related to the metalwork

Causality and expectedness of any SAEs will be confirmed by the Chief Investigator or another delegated surgeon co-investigator. SAEs that are deemed to be unexpected and related to the trial will be notified to the Research Ethics Committee (REC) and Sponsor.

All AEs will be reported to the TSC and DMC. Where repeated AEs of similar type are observed, these will be discussed with the DMC and will be onward reported should concerns be raised in relation to the type of event and/or frequency observed. All participants experiencing SAEs will continue to be followed up until the end of their participation in the trial. At the end of trial follow-up, all-cause mortality in study participants will be checked by authorised staff after securing the appropriate approvals using the electronically available NHS Summary Care Records or the National Care Records Service.

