### Objectives {7}

To investigate the clinical and cost-effectiveness of RSA versus HA for patients presenting with 3- and 4-part PHFs. Additionally, the effectiveness of surgery will be compared to non-surgical treatments (NS). The trial will:i.Undertake a randomised parallel group comparison to determine if RSA is superior to HA in treating 3- and 4-part PHFs based on change in the Oxford Shoulder Score (OSS) at 24-month post-randomisation.ii.Undertake a randomised parallel group comparison to determine if surgery is superior to NS in treating three- and four-part PHFs based on change in the OSS at 24 months.iii.Compare secondary outcomes of pain, range of motion, and OSS at 6 and 12 months between the trial arms using appropriate analytic models; describe and compare safety data including complications and adverse events between the trial arms.iv.Conduct a detailed economic evaluation to compare the cost-effectiveness of the comparisons described in objectives i and ii above at 24 months.v.Investigate the association of baseline characteristics (demographics, grip strength) with poor functional outcomes at 24 months.

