## Interventions

### Intervention description {11a}

Both surgical interventions (RSA and HA) will be performed under general anaesthesia and anterior (delto-pectoral) or superior (McKenzie type) surgical approaches may be used as per the treating surgeon’s usual practice. Along with the risks of general anaesthesia, both surgical interventions have potential risks and complications.

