#### Non-surgical treatment (NS)

Non-surgical treatment involves supporting the injured arm in a sling for a period of 3 weeks for comfort as in the PROFHER trial [8] and participants are provided with a sling care advice leaflet at the time of randomisation. The arm and shoulder are then gently mobilised under supervision of a physiotherapist with the aim of increasing the range of motion and performing active exercises as tolerated. Physiotherapy sessions are tailored and include advice and education on a home exercise programme predominantly based on daily functional tasks. The physiotherapy sessions include a combination of exercise, soft tissue techniques, joint mobilisations, stretching and relaxation techniques. The physiotherapy pathway for non-surgical treatment follows what was used successfully in the PROFHER trial [8]. As 3- and 4-part fractures will be included in this trial, we have allowed for a median of 12 physiotherapy sessions being required (compared to eight required in PROFHER). The exact treatments may be individualised to ensure that rehabilitation is tailored to individual needs in line with routine conservative care.

Non-surgical treatment has the advantage of avoiding the risks of anaesthesia and surgery. If pain is persistent or function remains poor after non-surgical treatment, delayed surgery may be performed at clinical discretion. This would not usually be considered before 6 months to allow an adequate period of rehabilitation to be pursued.

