## Assignment of interventions: blinding

### Who will be blinded {17a}

As the treatments cannot be adequately concealed, it is not possible to blind clinicians or participants to their treatment allocation. Trial statisticians analysing the data will not be blinded.

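### Adverse events must be related to the shoulder or a trial treatment, so recording of medical events named through anaesthesia depends on arm in the surgery v non-surgical comparison

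*Protocol article*

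**What the plan says.** All references are to the protocol article.

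Adverse event reporting and harms {22} sets two entry conditions for an AE. The event must be linked in time to the study treatment, and it must be one that "is related to the affected shoulder or to the study interventions or control treatments". After a list of shoulder and implant complications, the section adds a group of general medical events: "AEs associated with anaesthesia such as cerebrovascular events, cardiovascular events including venous thromboembolism, urinary retention and respiratory tract infection". It describes these as expected in this patient group.

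The same section defines a serious AE (SAE) by being unexpected and meeting a seriousness criterion. It states no relatedness condition. It then removes complications of anaesthesia or surgery, including thromboembolic events, from SAE status and treats them as AEs.

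On exposure, Intervention description {11a} says: "Both surgical interventions (RSA and HA) will be performed under general anaesthesia". The paragraph on non-surgical treatment (NS) says: "Non-surgical treatment has the advantage of avoiding the risks of anaesthesia and surgery". It allows delayed surgery at clinical discretion, usually not before 6 months.

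On use of the data, objective iii in Objectives {7} is to "describe and compare safety data including complications and adverse events between the trial arms". On who judges relatedness knowing the arm, Who will be blinded {17a} says that "it is not possible to blind clinicians or participants to their treatment allocation".

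**The concern.** Strokes, cardiac events, thromboembolism, urinary retention and chest infections occur in people aged 65 or over whether or not they have an operation. Randomisation would balance these background events between surgery and NS. The AE definition gives up that protection, because relatedness decides whether an event is recorded as an AE at all, instead of being a judgement attached to an event already recorded. The route by which these events become AEs is anaesthesia, which is open by allocation in two arms and normally closed in the third.

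At stake is the surgery v NS comparison of non-fatal medical events. Sample size {14} justifies a 6-point target difference for that comparison by the higher risks and costs of surgery, so readers will weigh the harms against the functional result. If NS events never enter the AE record, no later analysis of that record can recover them.

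**Working it through.** The plan gives no figure on this point, so the check is to follow one event through the definitions in each arm.

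**Step 1: trace the event.** Take a chest infection or stroke three weeks after randomisation that would have happened under any allocation.

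| | RSA or HA participant, after surgery | NS participant, no surgery |
|---|---|---|
| Related to the affected shoulder? | Usually no | Usually no |
| Related to a study or control treatment? | Can be attributed to the anaesthetic or operation | Usually not attributable to sling or physiotherapy |
| AE? | Yes, if so attributed | Usually no |
| SAE, if serious? | No, if classed as a complication of anaesthesia or surgery | Possible, if judged unexpected, since no relatedness is required |
| If fatal | In the all-cause mortality check | In the all-cause mortality check |

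An NS event can count as an AE in two situations: when it is judged related to the shoulder or to the control treatment (for example a thrombosis in the injured limb), and when it follows delayed surgery.

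The SAE route for NS participants is uncertain. If SAEs are read as a subset of AEs, or if the event is treated as expected because the section says so of these event types, a serious non-fatal NS event is counted nowhere. Non-serious events have no SAE route at all.

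**Step 2: separate bias from a real effect.** Let

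- b = background risk of the named events, equal in all arms by randomisation;
- t = additional risk truly caused by anaesthesia and surgery, all of it counted;
- pS, pN = probability that a background event is judged related, in surgery and in NS.

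Counted AE risk is t + b × pS in surgery and b × pN in NS. The difference is t + b × (pS − pN). The true effect is t, so the bias is b × (pS − pN). Events that surgery really caused are not bias. Only background events attributed to it are. If some truly caused events were judged unrelated and lost, that would act in the opposite direction.

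**Step 3: illustrate the size.** The documents give neither b nor the attribution probabilities. All inputs below are assumptions, and a difference of 1 is an extreme bound.

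| Assumed b | pS − pN = 0.25 | 0.50 | 1.00 |
|---|---|---|---|
| 2% | 0.5 | 1.0 | 2.0 |
| 5% | 1.25 | 2.5 | 5.0 |
| 10% | 2.5 | 5.0 | 10.0 |

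Entries are spurious percentage points, equivalently spurious events per 100 surgical participants. For example, 5% × 0.50 = 2.5. They are not converted to counts per arm. The printed 152/152/76 split belongs to the initial 2:2:1 ratio, which was later replaced by 1:1:1 for participants randomised to all three arms. The surgical totals also include dislocation patients who could not be allocated NS.

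**Step 4: the other comparisons.** In RSA v HA both arms have general anaesthesia and face the same filter, so pS is similar on both sides and the bias largely cancels. All-cause mortality, checked from NHS records, needs no attribution. The Oxford Shoulder Score models do not use AE counts.

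**The case against.** Limiting AEs to related events is a common and defensible choice in a pragmatic trial of established treatments. The rule is worded identically for every arm: an unrelated chest infection after RSA fails it too. Bias therefore needs misattribution, which the documents do not show.

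Other capture exists. Outcomes {12} lists complications and further procedures separately. The Appendix 2 schedule has complications, adverse events and resource use at 6, 12 and 24 months with no restriction by arm. The health economic section plans per-patient recording of other medical complications, inpatient episodes and primary care contacts.

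A reader might go further than the text allows, and infer that these events can never be counted in the NS arm, that the whole harms comparison is biased against surgery, and that this carries into the surgery v NS conclusion. The documents do not support this:

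- NS events count when related to the shoulder or control treatment or when they follow delayed surgery, and serious unexpected ones fit the SAE wording.
- The SAE exemption can push SAE counts against NS.
- Effectiveness is decided on the Oxford Shoulder Score, and the 6-point difference is a sample-size input that AE counts do not change.

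What remains is narrower. An identically worded rule does not act equally when one of its conditions can be met through an exposure that only some arms receive, and those who judge it know the arm. Equal visit schedules do not help when the definition decides what is counted. The economic data are collected for costing and are not stated to feed the AE comparison, although they suggest that a remedy is feasible.

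**Conclusion.** The point holds as arm-dependent ascertainment of non-fatal medical events in surgery v NS. AE counts lean against surgery to the extent that background events are attributed to it. SAE counts may lean the other way, because the exemption removes surgical complications from that category while a similar NS event can enter it. The net direction over all harms is therefore not fixed by the text.

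The size cannot be derived from the documents. The 0.5 to 10 point range rests wholly on the assumed background risks and attribution differences, and shows only that a noticeable artefact is possible. Because the stated definition itself creates the problem, this is not a detail left to an analysis plan. It should be corrected, but it does not threaten the primary outcome.

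**What to change.** Amend Adverse event reporting and harms {22} and the case report form as follows:

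- Record the medical events already named there in all three arms, whatever their judged relatedness, over one fixed window from randomisation (for example to the 6-month assessment), using the existing follow-up contacts.
- Compare surgery with NS on all recorded events of these types, among participants who could have been allocated NS. Primary analyses already uses that restriction for the Oxford Shoulder Score.
- Keep relatedness as a recorded descriptor, not an entry condition.
- Reconcile the AE and SAE definitions so that the same event is classified the same way in every arm.

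The cost is protocol and form wording plus a few more event forms, mainly in the NS arm. Timing is the real limit. Recruitment began in June 2018 and was expected to end on 30 June 2023, so the relevant contacts have passed for many participants, and a late change alone would make recording differ by recruitment date. For those participants the events would have to come from data already collected, such as hospital forms and resource-use questionnaires. If that is not possible, the surgery v NS comparison of medical AEs should be reported with this limitation stated.

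### The SAE definition mixes seriousness with expectedness and exempts surgical and anaesthetic complications even when fatal, so such a death is only an AE and escapes the notification rule

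*Protocol article*

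**What the plan says.** All the relevant rules stand in the protocol article under Adverse event reporting and harms {22}.

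- **Definition.** "Serious AEs (SAEs) are defined as any untoward and unexpected medical occurrence" that meets one of the usual outcome criteria, of which death is the first and threat to life the second.
- **Expected events.** A list of shoulder and implant complications is given as expected, and then: "AEs associated with anaesthesia such as cerebrovascular events, cardiovascular events including venous thromboembolism, urinary retention and respiratory tract infection can also be expected".
- **Exemption.** A further list opens with "the following are not considered a SAE but will be considered an adverse event". It has two entries: "Complications of anaesthesia or surgery (e.g., wound complications, infection, damage to a nerve or blood vessel and thromboembolic events" and "Secondary operations for infection; dislocation or instability; malunion; non-union; peri-prosthetic fracture; or for symptoms related to the metalwork".
- **Later assessment.** "Causality and expectedness of any SAEs will be confirmed by the Chief Investigator or another delegated surgeon co-investigator".
- **Notification.** "SAEs that are deemed to be unexpected and related to the trial will be notified" to the Research Ethics Committee and the sponsor.

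The same section sends all AEs to the TSC and DMC. It has repeated AEs of a similar type discussed with the DMC, and it checks all-cause mortality at the end of follow-up. Under Objectives {7}, objective iii is to "describe and compare safety data including complications and adverse events between the trial arms". Under Outcomes {12}, further procedures and complications are a secondary outcome.

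**The concern.** Seriousness describes what happened to the patient. Expectedness describes whether that kind of event was foreseen, and normally decides only how fast and to whom it is reported. The article makes the second a condition of the first, and adds an exemption that depends on the cause of the event and takes no account of its outcome.

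In a trial of two operations against non-surgical care, complications of surgery and anaesthesia are the serious events most plausibly caused by the allocated treatment. If they cannot be SAEs, two things suffer. A single fatal or life-threatening complication has no stated route to the ethics committee or sponsor. And a count of SAEs by arm, which readers of a trial report take as a summary of serious harm, would leave out serious harm from surgery.

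**Working it through.** The article states no figure on this point, so the check is to follow example events through its rules.

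1. **Fatal thromboembolism after surgery.** Death meets a seriousness criterion. But venous thromboembolism is listed among the expected events associated with anaesthesia, so the event is not unexpected and fails the definition. Thromboembolic events are also named in the first exemption, so it fails a second time. Result: AE.
2. **Fatal anaesthetic complication of a kind not listed anywhere.** This is unexpected and meets the death criterion. But the bracket in the first exemption only gives examples, so the class is all complications of anaesthesia or surgery, and no outcome is carved out. Result: AE.
3. **Readmission and reoperation for peri-prosthetic fracture.** The indication is on the second exemption list. Result: AE.
4. **Reoperation for an indication not on that list.** The second exemption does not apply, and the event is judged on the definition. It may be an SAE.
5. **Operation for non-union or malunion in the non-surgical arm.** These indications are on the list, so the event may also be exempt there. Delayed surgery for pain or poor function, which the section Non-surgical treatment (NS) allows, is not on the list.

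Cases 1 and 2 show two independent obstacles. Deleting the word unexpected would still leave case 1 exempt. Removing the exemption alone would leave case 1 outside the definition.

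**Internal consistency.** If every SAE is unexpected by definition, confirming the expectedness of SAEs afterwards decides nothing, and the word unexpected in the notification sentence is redundant. Those later sentences make sense only if an SAE can be expected, which the definition rules out.

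**Notification.** The rule acts on SAEs only. Cases 1 to 3 never become SAEs, so it does not reach them, however clearly they are related to treatment.

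**Possible size.** The article gives no serious-event rates, so these are assumptions. Let b be the background rate of serious events that count as SAEs, and s the rate of serious surgical or anaesthetic complications, all exempt, with no overlap. The share of serious events in a surgical arm that would not count is s / (b + s):

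| b | s = 2% | s = 5% | s = 10% |
|---|---|---|---|
| 3% | 2/5 = 40% | 5/8 = 63% | 10/13 = 77% |
| 5% | 2/7 = 29% | 5/10 = 50% | 10/15 = 67% |
| 10% | 2/12 = 17% | 5/15 = 33% | 10/20 = 50% |

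If the non-surgical arm had rate b and no such complications, the ratio of all serious events, (b + s) / b, would run from 12/10 = 1.2 to 13/3 = 4.3. The ratio of countable SAEs would be b / b = 1.0. This shows how an SAE table could mislead. It is not an estimate for this trial.

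**The case against.** The strongest reply is that nothing is lost. The exempt events are AEs by the very sentence that exempts them. They therefore enter the comparison in objective iii, which covers complications and adverse events and names no separate SAE comparison. Further procedures and complications are collected at 6, 12 and 24 months (Appendix 2), all AEs go to both committees, and the mortality check finds deaths whatever their label. The article also does not say that seriousness goes unrecorded for AEs. Form fields are detail that an article may leave to the full protocol.

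Most of that stands, and it rules out several stronger readings that a reader might infer:

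- *The trial's safety comparison is biased towards surgery.* The documents do not support this. The stated comparison includes the exempt events. Even for an SAE table, the direction depends on which background events count. The AE definition is limited to events related to the affected shoulder or the study treatments, and it is unclear whether unrelated hospitalisations count as SAEs in any arm.
- *All reoperations are exempt.* Only those for listed indications are, and some of these can arise without initial surgery.
- *The complication rate of up to 24% after RSA, cited in the Background, measures the problem.* It covers minor as well as major complications and is an upper figure. Applying it to the planned 152 per surgical arm would also use numbers from the 2:2:1 ratio, which was later replaced.

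The reply does not repair the classification. The committees are guaranteed to meet only once a year. The stated trigger for discussion and onward reporting is repeated AEs of a similar type, which a single death does not meet. The mortality check comes at the end of follow-up, and no attribution to treatment is stated.

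**Conclusion.** The point holds as a fault of classification and reporting route. The definition contradicts the later expectedness and notification sentences. As written, a fatal, life-threatening or disabling complication of surgery or anaesthesia is an AE only, outside notification to the ethics committee and sponsor. Any SAE table by arm built on this definition would leave out serious surgical harms.

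These conclusions rest on the wording alone. The size does not: the range of 17% to 77% of surgical-arm serious events uncounted follows wholly from assumed rates. The primary outcome is unaffected, and so is the stated comparison of complications and AEs. The change is still worth making, because it concerns prompt oversight of the gravest events and is cheap.

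**What to change.** Reconcile the definition, the exemption list and the notification sentence in section {22}:

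1. Remove the requirement that an SAE be unexpected, so that seriousness is defined by outcome only. Keep expectedness as the later assessment that the section already provides.
2. Recast the exemption as one from expedited reporting only, and state that it does not apply to deaths or life-threatening events.
3. Make the notification sentence agree, and say how expectedness is judged when a listed type of event is fatal or life-threatening. Otherwise case 1 would become an SAE and still not be notified.
4. Classify seriousness for every recorded AE, retrospectively where needed, and report serious events, including surgical complications, by allocated arm.

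The cost is a wording amendment, slightly more SAE processing, and some retrospective reclassification. Recruitment began in June 2018 and was due to end in June 2023 (Trial status), so several years of events are involved. They are already recorded as AEs, and applying the revised classification to all of them avoids having two definitions in one trial.
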